#### Replacements

Replacements will be enlisted if participants need to withdraw prior to their TKA taking place. To maintain the randomization ratio of 1:1, the replacement would be allocated to the same treatment arm of the withdrawn participant.

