### Sample Size

#### Sample Size Estimation and Justification

##### Stage 1

We will initially involve 5 individuals who have undergone a TKA within the last 5 years to take part in video alpha testing encompassing the understandability and actionability of the prototype of the educational videos. Content analysis will be via an inductive approach [60]. If we find that the issues identified in the prototype videos differ substantially between each participant and saturation of the feedback content is not occurring, we will enroll 5 further individuals to undertake the alpha testing, such that feedback from up to 10 individuals will be included in stage 1. The purposive sampling approach being adopted will enable a diverse group of viewpoints to be derived. Taken together with the collaborative approach between the stakeholder groups involved in the design component of this study, we are confident that the number of participants involved in the alpha testing is sufficient to support the development of education materials to be further evaluated in stage 2 of this study.

##### Stage 2

A sample of 150 individuals who have been identified as requiring a TKA by their treating orthopedic specialist (2 subgroups of n=75) will be recruited. This will allow for expected dropouts (approximately 22/150, 15%) and ensure a minimum sample size of 64 for each group, which will enable the study to be adequately powered (see calculations below). A screening log will be kept and will collate reasons why any participants were screened but did not take part in the study.

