### Power Calculation: Sample Size Estimate

The number of participants was selected based on previously published findings using the Hospital for Special Surgery Total Knee Replacement Expectations Survey (HSS-TKR) as our primary outcome measure to demonstrate a clinically meaningful change in the overall patient expectation score [35]. Mancuso et al [35] describe a clinically meaningful change in expectations to be associated with a 6-point change in transformed HSS-TKR total scores. To determine a significant difference between 2 groups of patients, such that α=.05, power 80%, and SD 12, will require 64 patients per group. In this study, we will enroll 75 patients per treatment arm to allow for any potential loss of participation at the follow-up time points.

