### Randomization Procedures

#### Block Randomization

To ensure a balance in the sample size for each treatment arm during the participant recruitment phase, we will apply block randomization [59]. For a total of 150 recruited participants, we will generate 38 blocks of 4 participants per block with a 1:1 allocation ratio between the intervention and control arms. The randomization list and block allocation details will be generated using software provided by Sealed Envelope Ltd (2022)[] .

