#### Stratification

We recognize that the level of standard clinical care, with respect to the scope and format of educational materials provided to patients undergoing TKA, may vary significantly between health care providers represented in the recruitment sites involved in the study, and this may influence expectations set by participants. In light of this, we will include “health care provider” as a stratification variable.

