### Secondary Outcomes

The following secondary outcomes will also be evaluated:

The number of participants who decide not to proceed with their TKA.The level of patient expectation fulfillment derived from the HSS-TKR questionnaire, the DQO Index, and activity expectations, conducted 6 months after the TKAThe level of patient satisfaction with surgical outcomes assessed at 6 months after the TKA.A change in patient health literacy (within individual patients’ scores), derived from the HLS-EU-Q12, conducted at study entry and at 6 months after the TKA

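### Replacements for participants who withdraw before TKA are put in the withdrawn participant's arm by rule instead of being randomised, which makes their allocation predictable and opens the primary comparison to selection bias

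*Protocol article*

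**What the plan says.** The Replacements paragraph (Randomization Procedures) sets both the trigger and the allocation. The trigger is "Replacements will be enlisted if participants need to withdraw prior to their TKA taking place". The allocation, with its stated reason, is "To maintain the randomization ratio of 1:1, the replacement would be allocated to the same treatment arm of the withdrawn participant".

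The same part of the article describes the main allocation differently. Block Randomization provides "38 blocks of 4 participants per block with a 1:1 allocation ratio between the intervention and control arms". Under Stratification, "we will include “health care provider” as a stratification variable", because standard education may differ between providers and may influence expectations.

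Losses are already provided for. The Stage 2 sample size paragraph says of the 150 patients: "This will allow for expected dropouts (approximately 22/150, 15%) and ensure a minimum sample size of 64 for each group".

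Three other places bear on the point:
- **Timing.** Stage 2 puts the post-intervention assessment, which supplies the primary outcome, 3 weeks before TKA.
- **Not proceeding.** Secondary Outcomes lists "The number of participants who decide not to proceed with their TKA". Proceeding With TKA puts the question to all participants, and Feedback Survey collects information from those who did not have surgery.
- **Withdrawn data.** Recruitment and Enrollment Procedures and Informed Consent let a withdrawing participant choose whether data already collected are used or removed.

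**The concern.** Randomisation protects the comparison because nobody enrolling a patient can foresee the arm. The replacement rule gives that up for every replacement. Withdrawing participants are asked to notify the research team, and a member of that team telephones each eligible patient about taking part. Once someone has left, the arm waiting for the replacement can be worked out before the next patient is approached. One arm receives videos and the other standard care alone, and the primary outcome is a self-reported expectations survey. A choice of whom to approach, or how keenly, could therefore carry through to the result.

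Two features add to the problem. First, the replacement window runs up to surgery, although the primary outcome is taken 3 weeks earlier, so someone who has already given primary data can still be replaced. Second, the paragraph does not separate leaving the study from deciding against surgery. The plan treats the latter as a possible result of the education, so the trigger must not overlap with it.

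As written, the rule also does not tie the replacement to the provider of the person who left, so it can disturb the balance that the stratification is meant to secure.

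**Working it through.** **1. The plan's own sample size.** Inputs from Power Calculation: difference 6 points, "such that α=.05, power 80%, and SD 12, will require 64 patients per group".
- Normal approximation, two-sided: n = 2 × (1.96 + 0.84)² × 12² / 6² = 62.8, so 63 per group.
- Two-sample t test: 63.77, rounded up to 64. The plan's figure reproduces. A one-sided test would give 50, so the plan is two-sided.
- Dropout: 150 − 22 = 128 = 2 × 64, and 22/150 = 14.7%, which the plan rounds to 15%.

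**2. Is replacement needed for power?** Two-sample t test, 6 points, SD 12, 75 randomised per arm, nobody replaced:

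| Loss | Left per arm | Power |
|---|---|---|
| 0% | 75 | 0.86 |
| 5% | 71.25 | 0.84 |
| 10% | 67.5 | 0.82 |
| 15% | 63.75 | 0.80 |

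The existing allowance keeps the planned power. Exact 1:1 is not needed either: 60 against 68 completers has an effective size of 2 × 60 × 68 / 128 = 63.75 per arm, with power again about 0.80.

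**3. How many allocations could be non-random?** If every expected dropout fell before TKA and was replaced, 22 / (150 + 22) = 22/172 = 13%. With 5% or 10% replaced, the share is 0.05/1.05 = 5% or 0.10/1.10 = 9%. The article gives no figure for losses before TKA.

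**4. What could that do to the primary test?** Assumptions, not taken from the article: no true effect, SD 12, 75 analysed per arm, and replacements in the two arms differing by s points because of selective enrolment. The replaced patients are not analysed. Type I error at nominal 0.05, from 20,000 simulated trials per cell:

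| Share replaced | s = 0 | s = 6 | s = 12 |
|---|---|---|---|
| 5% | 0.048 | 0.054 | 0.059 |
| 10% | 0.049 | 0.060 | 0.093 |
| 15% | 0.049 | 0.070 | 0.138 |

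The bias at 15% (11 of 75 per arm) is 11/75 × 6 = 0.9 points or 11/75 × 12 = 1.8 points, against a target of 6. If the withdrawn participants also stay in the analysis with their primary data, it falls to 11/86 × 6 = 0.8 or 11/86 × 12 = 1.5.

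The s = 0 column matters most for reading the rest: filling a place in the same arm does not by itself inflate the error rate. Damage comes only through s, or through exclusion of the people replaced.

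**The case against.** Several points can fairly be made for the plan.

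- **Withdrawal is not the same as declining surgery.** The rule speaks of withdrawing. The article asks everyone whether they will proceed, collects information from those who do not, restricts only the 6-month fulfilment and satisfaction measures to those operated on, and counts non-proceeders as an outcome. A reader might infer that the rule removes non-proceeders and so spoils that count. The documents do not support this: they point to non-proceeders staying in the study. What stands is that the Replacements paragraph does not draw the line itself.
- **Replaced participants need not leave the analysis.** A reader might also infer that patients whose expectations changed most are swapped out and the effect estimate distorted. No passage says that replaced participants are excluded, and those who withdraw may let their data be used.
- **Foreknowledge is possible, not shown.** The article does not say who assigns replacements. The rule makes the arm predictable; it does not show that anyone acts on it.
- **The allowance and the replacements may cover different losses.** Power Calculation links the 75 per arm to loss at the follow-up time points, which can include the 6-month visit. Replacement covers only the period before surgery, at most 6 weeks. The 13% is therefore a ceiling, and a charge of double compensation would go too far.

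These points narrow the consequence. They do not justify the rule, since a replacement could be drawn from the list just as easily. Nor can the rule be read as detail left to a fuller document: the article states it outright.

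**Conclusion.** The concern holds in this limited form. The plan fixes a non-random, predictable allocation for replacements. It departs from the article's own blocked and stratified scheme and is not needed for power. At most 13% of allocations would be affected, and only if all expected dropouts occurred before TKA.

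The effect on the primary comparison is a risk whose size depends on assumptions the article cannot settle. It is nil with no selective enrolment and no exclusion of those replaced. In the illustrations at 15% replaced, type I error reaches 0.07 for a 6-point selection difference and 0.14 for a 12-point one. It cannot be concluded that the primary result or the count of non-proceeders is corrupted. The change should still be made, because non-random allocation cannot be repaired at analysis.

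**What to change.** 1. Delete the same-arm rule. Randomise 150 and rely on the existing allowance. If more participants are wanted to offset losses, give each the next unused place on the randomisation list for that patient's provider, whichever arm it holds. The list has 38 × 4 = 152 places, so it would need spare blocks per provider, prepared in advance.
2. State that all randomised participants are analysed in their allocated arm, and that a post-intervention HSS-TKR already given is used even if the participant later withdraws, unless that person asks for the data to be removed.
3. State that not proceeding with TKA is an outcome and not a withdrawal, and that all randomised participants form its denominator.

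The cost is a short amendment. Relying on the allowance needs no extra patients. The final arms may differ by a few patients, which at 60 against 68 still leaves power at about 0.80.

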### Data Collection Tools and Procedures

#### Online Data Collection and Centralized Data Repository

##### Screening logs

Screening logs will be maintained for all potential candidates being recruited to the study and will contain identifiable patient information. The file will be stored online as a password-protected file on the secure University of Newcastle server.

##### Deidentification of Patient Information

All consented participants will be allocated a study code comprising a patient ID number and their initials. All data collected in the study will be identifiable by the study code and remain deidentified during the data collection and analysis phases of the study.

##### Data Collection Platform

Study data will be collected and managed using the REDCap (Research Electronic Data Capture; Vanderbilt University) tools hosted at the Hunter Medical Research Institute [61,62]. REDCap is a secure, web-based software platform designed to support data capture for research studies, providing (1) an intuitive interface for validated data capture, (2) audit trails for tracking data manipulation and export procedures, (3) automated export procedures for seamless data downloads to common statistical packages, and (4) procedures for data integration and interoperability with external sources.

REDCap study-specific access will be established, allowing secure access by the research team with all assessment tools formatted as online forms to enable direct data entry by the study participants. Participants will be sent an email from REDCap containing an encrypted link to their forms for completion. If participants request to complete hard copies of forms, these will be generated and posted to the participant by the study team, with the completed form data subsequently entered into the REDCap platform by a member of the study team.

Forms will be disseminated for completion at 3 distinct time points–prior to their TKA at study entry (baseline), following the education intervention, and 6 months following their TKA, as shown in Table 1.

**Table 1. T1:** Assessments to be undertaken in the randomized controlled trial and frequency of collection.

Measure (tools)		Study time points		
		Baseline	Post intervention	6 months post TKA^a^
Clinical and demographic details				
Patient-reported age, sex, highest level of education achieved, employment status, and diagnosis		✓		
Comorbidities				
Charlson Comorbidity Index [63]		✓		✓
Knee symptomology				
12-item short-form for the Knee Injury and Osteoarthritis Outcome Score [64]		✓		✓
Oxford Knee Score [65]		✓		✓
Forgotten Joint Score [66]				✓
Mood status (depression, anxiety, and stress)				
21-item Depression, Anxiety and Stress Scale [67,68]		✓		✓
Quality of life				
EQ-5D-5L [69]		✓		✓
Health literacy				
12-item European Health Literacy Survey Questionnaire [53]		✓		✓
Expectations				
Hospital for Special Surgery Total Knee Replacement Expectations Survey [34]		✓	✓	
Direct Questioning of Objectives Questionnaire Index [70]		✓	✓	
Activity expectations [30]		✓	✓	
Expectation fulfillment				
Hospital for Special Surgery Total Knee Replacement Expectations Survey				✓
Direct Questioning of Objectives Questionnaire				✓
Activity expectation satisfaction				✓
Satisfaction with outcomes				✓

a TKA: total knee arthroplasty.

### Study Questionnaires

#### Comorbidities

We will use the Charlson Comorbidity Index, which provides a weighting to concomitant health conditions based on the nature of the condition and age of the individual and is used to predict 1-year mortality. The higher the score, the higher the mortality risk. We will apply the same 10 medical conditions and weightings used by Chaudry et al [63]. Participants will be asked to indicate if they experienced any of the 10 medical conditions provided, at study entry and at 6 months after TKA.

#### Knee Symptomology and Function

Symptomology of the affected knee that will undergo TKA will be assessed using the 12-item version of the Knee Injury and Osteoarthritis Outcome Score (KOOS-12) [64]. KOOS-12 is a 12-item measure derived from the original 42-item KOOS. KOOS-12 contains 4 KOOS pain items, 4 KOOS function (activities of daily living and sport/recreation) items, and 4 KOOS quality of life. Each item is rated using a 5-point Likert scale from 0 to 4, left to right, with 0 representing no knee problems and 4 representing extreme knee problems [64]. Items with lower scores are indicative of lesser symptoms, and higher scores reflect worse symptomology. Participants will be asked to complete a copy of this questionnaire at study entry and at 6 months after their surgery.

We will also apply the Oxford Knee Score (OKS) [65]. The OKS is a patient-reported outcome measure that consists of 12 questions about an individual’s level of function, activities of daily living, and how they have been affected by pain over the preceding 4 weeks, before and after a total knee replacement. Each item is rated using a 5-point Likert scale from 0 to 4, with 0 representing no knee problems and 4 representing extreme knee problems [65]. Items with lower scores are indicative of lesser symptoms, and higher scores reflect worse symptomology. In this study, the OKS will be applied at study entry and at 6 months after their surgery.

At 6 months following TKA, we will apply the Forgotten Joint Score (FJS) [66]. The FJS is a 12-item questionnaire concerning the participants’ awareness of their artificial joint during activities of daily life [66]. For each question, the participant can choose between 6 response options, namely never (0 points), almost never (1 point), seldom (2 points), sometimes (3 points), and mostly (4 points). The summation of the scores is then divided by the number of items responded to. The mean score is multiplied by 25 to give a score from 0 to 100, which is then subtracted from 100. Larger scores are indicative of greater “forgetting” of the artificial joint.

#### Mood Status

The mood status of our study participants will be assessed using the 21-item Depression Anxiety Stress Scales (DASS-21) [67]. The full DASS and abbreviated DASS-21 have been validated to measure the 3 negative emotional states (ie, depression, anxiety, and stress) in research and clinical settings [68]. Each of the DASS-21 subscales contains 7 items. Participants will be asked to use 4-point severity/frequency scales to rate the extent to which they have experienced each state over the past week. Scores for depression, anxiety, and stress will be calculated by summing the scores for the relevant items. Higher scores are indicative of higher levels of symptoms. All scores derived from the 21-point scale will be multiplied by 2 to enable comparison to the full 42-point DASS and determine clinical cutoffs for symptom severity. In this study, participants will be asked to complete the DASS-21 questionnaire at study entry (prior to their TKA) and at 6 months after their surgery.

#### Quality of Life

The EQ-5D-5L was developed to describe and value health status across a wide range of disease areas [69]. The tool contains a short descriptive system of the respondent’s health status and a visual analog scale to summarize health status (EQ-VAS). The descriptive system contains 5 dimensions, including mobility, self-care, usual activities, pain/discomfort, and anxiety and depression. Participants will choose the most appropriate severity of each dimension on a 5-point scale ranging from “no problems” to “unable to / extreme problems. A summary EQ-5D index score will be derived using dimension weightings from recent value sets described for the Australian population [71]. The EQ-VAS provides an overall current health rating score ranging from 100 (the best health) to 0 (the worst health). In this study, participants will be asked to complete the EQ-5D-5L questionnaire at study entry (prior to their TKA) and at 6 months after their surgery.

#### Health Literacy

Health literacy is defined as the degree to which individuals can obtain, process, understand, and communicate about health-related information needed to make informed health decisions [72]. In this study, we will assess participants’ health literacy using the shortened version of the HLS-EU-Q12 [53]. Participants will be presented with a number of competencies encompassing information relating to health care, disease prevention, and health promotion and covering 4 cognitive domains, including proficiency in accessing, understanding, appraising, and applying health information. Respondents will rate the level of difficulty in undertaking each competency on a 4-point scale ranging from 1 (very difficult) to 4 (very easy), with higher total scores indicative of higher health literacy. In this study, participants will be asked to complete the HLS-EU-Q12 at study entry (prior to their TKA) and at 6 months after their surgery.

#### Expectations

As there is no current gold standard for characterizing patient expectations of TKA outcomes, we will be adopting a mixed methods approach and using both standardized self-report, closed-response surveys and open-ended questions to quantify patient expectations and changes in these expectations over time. To evaluate the change in expectations, all participants will be asked to complete the following questionnaires at study entry and following the intervention.

#### Hospital for Special Surgery Total Knee Replacement Expectations Survey

The HSS-TKR [34] is a closed response survey, which enables respondents to provide ratings for the importance of 17 common patient expectations of outcomes following TKA, including pain, physical function, and psychological items. Importance ratings range from 1 (very important) to 5 (does not apply). The survey quantifies the level of importance of common knee replacement patient expectations and has been applied in numerous studies [73].

#### Direct Questioning of Objectives Questionnaire

Methods comparable to those applied by Karunaratne et al [70], using open-ended questions related to participant expectations, will be applied. Participants will be asked to list at least 1 and up to 5 of their most important expectations of TKA surgical outcomes, and then an assessment will be given for two domains for each expectation on 11-point numerical rating scales: (1) the importance of each expectation and (2) the current ability to achieve the task / item. The reported values for importance and ability will be interpreted as “low” if ≤5, and “high” if ≥8. A Direct Questioning of Objectives Questionnaire Index (DQO Index) will be derived from the product of the score for each domain.

#### Activity Expectations

We will use an open-ended question to identify participant expectations relating to their most important activities they want to undertake following TKA [30]. Participants will be asked to identify 3 activities important to them to achieve following the TKA by responding to the following question:

*What activities are you hoping to be able to do after your knee surgery that you cannot do now? (eg this could be an everyday life activity, employment or work activity, social activity, specific movement / motion or exercise etc.)*

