Social, demographic, and cultural factors also influence the nature and scope of patient expectations [26-28]. A comparative study of patients in the United Kingdom, United States, and Australia revealed that while overall satisfaction rates were similar, Australian patients were more likely to expect improved function at 12 months post surgery and placed greater emphasis on recreational activities and unaided mobility [29]. Our recent research in an Australian cohort further demonstrated that the majority of patient expectations centered on high-impact activities, such as golf, cycling, long-distance walking, and gym-based exercise [30].

Despite the importance of patients setting realistic expectations to optimize expectation fulfillment [31-33], this issue is not routinely addressed in clinical practice, partly due to the lack of standardized methods for assessing expectations and their fulfillment. Some studies have focused narrowly on pain reduction and basic functional outcomes, omitting patient-specific goals [21]. Others have used predefined activity lists to gauge importance [34]. However, no gold-standard approach currently exists for characterizing and evaluating patient expectations from TKA.

Despite the lack of a standardized approach, several groups have suggested approaches to assess patient expectations. One approach involves patient-reported surveys that categorize expectations by importance preoperatively and assess fulfillment postoperatively [34,35]. This method allows for structured quantification of expectation levels and categories. A more recent alternative is inductive content analysis, which uses open-ended questions to capture patient-specific expectations without the constraints of predefined categories [36], which enables a more personalized understanding of patient expectations and their fulfillment.

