While patient expectations can certainly be assessed, the more critical challenge lies in actively shaping those expectations so that patients are positioned to be highly engaged in their recovery and ultimately satisfied with their outcomes. Achieving this requires more than simple information sharing—it calls for deliberate, structured patient education. However, despite its importance, such education is often underemphasized or even absent in current presurgical discussions. Indeed, preoperative education aimed at modifying expectations has shown promise in enhancing patient satisfaction [35,37]. Such interventions help patients set realistic goals, leading to reduced expectation levels and improved fulfillment at 12 months post surgery [37]. In addition, targeted education has been shown to reduce the number of expectations compared to standard education alone [35]. Collectively, these findings support the integration of expectation management into preoperative care to optimize patient outcomes.

Musculoskeletal health literacy among patients seeking orthopedic care has been found to be lower than general health literacy [38]. While there is a substantial volume of online information regarding TKA, its utility is limited due to poor readability, understandability, and actionability [39]. This is concerning, as low health literacy is associated with patients with musculoskeletal conditions setting lower expectations for surgical outcomes [40-42].

Structured educational interventions have demonstrated efficacy in improving health literacy. Even a single structured session has been shown to enhance health literacy among patients with orthopedic conditions [43]. Furthermore, eHealth education has shown promise in improving both health literacy and self-efficacy in older adults [44]. Despite these encouraging findings, uptake of educational resources related to TKA rehabilitation and recovery remains limited [45].

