##### Overview

The educational materials to be developed will consist of multiple videos that patients will access online. Each video developed will run for no more than 5 minutes and address different aspects of recovery and capacity to undertake a range of different tasks and activities following TKA surgery.

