#### Expectation Fulfillment

The level of expectation fulfillment or satisfaction to undertake goals identified will be determined at 6 months after TKA for participants who proceeded with surgery.

For the HSS-TKR items, participants will be asked to indicate the extent of fulfillment of the expectations, identified prior to surgery, using a 5-point Likert scale, ranging from 5 (completely) to 1 (not at all).

The DQO Index will be repeated post TKA, and differences with values obtained prior to TKA will be indicative of the ability to achieve the task.

For activity expectations identified in the pre-TKA assessment, participants will be asked to rate how satisfied they were that each activity could be undertaken using a 7-point Likert scale ranging from 1 (completely dissatisfied) to 7 (completely satisfied).

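### Open-ended expectations are elicited with no time horizon but assessed once at 6 months, so a goal not yet due cannot be told apart from one that failed

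*Protocol article*

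**What the plan says.** All references are to the protocol article.

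- **Activity Expectations** prints the question in full: "What activities are you hoping to be able to do after your knee surgery that you cannot do now". Three activities are requested. The only time reference is that they come after surgery.
- **Direct Questioning of Objectives Questionnaire**: "Participants will be asked to list at least 1 and up to 5 of their most important expectations of TKA surgical outcomes". Each is rated for importance and current ability on 11-point scales, and the index is the product of the two. No date is mentioned. The exact form is not shown.
- **Expectation Fulfillment** fixes the assessment: "The level of expectation fulfillment or satisfaction to undertake goals identified will be determined at 6 months after TKA". For activities, "participants will be asked to rate how satisfied they were that each activity could be undertaken using a 7-point Likert scale". For the other instrument, the index is taken again after surgery and its change from the presurgical value is read as the patient's ability to reach the goal.
- **Table 1** has both instruments completed at baseline and after the intervention, then once more at 6 months. **Secondary Outcomes** lists fulfilment from both at 6 months.
- **Data Analysis, Stage 2** relates fulfilment to overall satisfaction, using Spearman coefficients for the activity ratings.
- **Background** mentions 12 months twice: "Australian patients were more likely to expect improved function at 12 months post surgery", and, for earlier education programmes, "leading to reduced expectation levels and improved fulfillment at 12 months post surgery".

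**The concern.** Fulfilment is a comparison of what was expected with what happened, and it needs both on the same clock. Here the expectation has no date and the result is read at 6 months. Background says that goals in an Australian cohort centre on demanding pursuits such as golf and cycling, so some patients could reasonably have a longer period in mind. At 6 months such a patient may be on course, yet the record would look much like that of a patient whose goal had failed.

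The programme exists to change expectations, and expectations are elicited again after it. The arms could therefore come to list goals with different implicit horizons. Expectation fulfilment is a named secondary outcome and a stated aim, and it feeds the fulfilment-satisfaction correlation. The missing information is never collected, so an analysis plan cannot repair this afterwards.

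**Working it through.** **The protocol's own figure.** The only relevant stated figure is the sample size for the primary outcome (Power Calculation): difference 6, SD 12, alpha 0.05 (two-sided assumed), power 80%, 64 per group.

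- Normal formula: n = 2 × (1.960 + 0.842)² × 12² / 6² = 62.8, so 63.
- Two-sample t version: 63.77, so 64. Power at 64 per group is 80.1%.

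The stated figure reproduces. It concerns the presurgical change in the HSS-TKR score and does not depend on the open-ended items. The protocol gives no figure for fulfilment.

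**Expectation and assessment side by side.**

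| Instrument | Date in prompt | Assessed | What is recorded at 6 months | Expected date recorded |
|---|---|---|---|---|
| Activity question | none (wording printed) | 6 months, once | satisfaction, 1 to 7 | no |
| DQO | none described | 6 months, once | index repeated; change from the presurgical value | no |

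On the DQO, a goal not yet due shows little gain because the index uses current ability. On the activity item the effect depends on how the patient rates an activity that is on course but not yet reached.

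**What this could do to an arm comparison.** The protocol gives neither the share of late goals nor any score distribution, so the following inputs are assumptions. Let q be the share of goals with a horizon beyond 6 months:

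arm mean = (1 − q) × score of due goals + q × score of late goals.

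Take 5.5 for due goals and 3.0 for late goals on the activity scale.

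- q = 20% in both arms: 0.8 × 5.5 + 0.2 × 3.0 = 5.0 in each; difference 0.
- q = 20% control, 40% intervention: 5.0 against 0.6 × 5.5 + 0.4 × 3.0 = 4.5; difference −0.5.
- The same shares with a true gain of 0.3 on due goals in the intervention arm: 0.6 × 5.8 + 0.4 × 3.0 = 4.68; difference −0.32.
- q = 40% control, 20% intervention, no true gain: 4.5 against 5.0; difference +0.5.
- Late goals rated 4.0 instead of 3.0, no true gain: the two unequal cases become 5.2 against 4.9 (−0.3) and 4.9 against 5.2 (+0.3).
- Late goals rated as highly as due ones (5.5), no true gain: difference 0 whatever the shares.

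The sign follows the arm with more late goals, and the size follows how patients rate them. The protocol fixes neither.

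**Which list is scored.** Expectation Fulfillment refers to activities named in the presurgical assessment, but there are two such assessments. If the baseline list is scored, the goals were written before the intervention, and randomisation balances their type and initial horizon. If the post-intervention list is scored, the horizons can differ by arm because of the programme.

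**The case against.** The strongest reply is that nothing here is scored as met or unmet. The activity item rates satisfaction, and a patient who knows that a goal is due later may rate it well. The DQO measures a change, not a failure. This stands, and it limits the claim to ambiguity plus a tendency to understate DQO ability gains.

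A reader might go further and infer that late goals count as poor fulfilment and that a programme teaching recovery times would look harmful. The protocol does not support this, for four reasons.

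- The videos are said to "address different aspects of recovery and capacity to undertake a range of different tasks and activities following TKA surgery". Recovery times are not mentioned. Steering patients to more achievable goals could equally shorten their horizons and flatter the programme. A programme patient who has learned to wait might also be more satisfied at 6 months than a control patient.
- The 12-month references in Background do not show that goals in this trial fall due after 6 months. One concerns improved function in a comparison of countries, and the other is the time at which a cited study reported fulfilment. The demanding activity goals come from a separate cohort with no date given.
- An illustration in percentages of goals met would describe an endpoint that this trial does not use.
- Overall satisfaction is a separate global question about the result of the operation and is not derived from the listed goals.

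It is also fair that the exact DQO wording is not shown, so its prompt could contain a date. The activity question is printed in full and does not. None of this removes the core gap: one assessment time, no date in the prompts as given, and no expected date recorded.

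**Conclusion.** The concern holds in a limited form. As described, the two open-ended instruments cannot distinguish a goal that failed from one not yet due at 6 months. The secondary fulfilment results based on them, and their association with satisfaction, are ambiguous for that reason.

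A bias between arms is possible but not established. It requires that the post-intervention list is scored, that the share of late goals differs by arm, and that patients rate late goals lower. Its direction is open and its size cannot be computed from the protocol; the range of −0.5 to +0.5 above rests wholly on assumed inputs. If baseline goals are scored, what mainly remains is ambiguity in both arms, with DQO gains understated against the patients' own horizons.

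The primary outcome, its sample size and the global satisfaction item as measured are untouched. This is a cheap improvement to secondary outcomes, not a flaw in the main comparison.

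**What to change.** Before recruitment, do one of the following at both presurgical assessments:

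1. Add 'by 6 months after your knee surgery' to the activity question and to the DQO prompt; or
2. Keep the wording, add one field per goal for the date by which the patient expects to reach it, and analyse goals due by 6 months separately.

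In either case, state whether the baseline or the post-intervention list is scored at 6 months. If option 2 is combined with the post-intervention list, the subset of goals due by 6 months is itself open to influence by the programme, so its arm comparison should be read with that in mind.

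Leave the HSS-TKR forms unchanged. Do not add a response such as 'not yet, I still expect this'. It would let missed goals leave the unmet group, possibly at different rates by arm, and it does not fit an ordinal scale.

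The cost is a few words or one field on a form. Option 1 slightly reduces comparability with the team's earlier use of the activity question and captures longer-term goals less well. A 12-month assessment is not a ready alternative: Results has recruitment running to September 2026 and final results by April 2027, and a patient recruited in September 2026 could not reach 12 months after surgery before September 2027.
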